#### 2- user registration

Having reviewed the course contents, the professional will be requested to register with the data collection platform.

#### 3-platform

Finally, via this icon, access to the data collection base is granted, using a username and personal password, to start inputting cases (units of analysis).

### Unit analysis sample

#### Sample size

In a second stage the units of analysis are recruited. A sample of 1708 women is established (Table 2). The calculation was performed using the EPIDAT program to test hypotheses in a model of comparison of proportions in independent groups. A possible loss of 25% of the sample is estimated, and so by applying the correction factor where R is the expected proportion of losses, the following sample size is finally envisaged:

**Table 2 Tab2:** Study sample size calculated using the EPIDAT program

Power (%)	Sample size^*^ (+ correction factor for expected losses)		
	EG	CG	Total
80.0	854	854	1708

Sample sizes to apply the χ2 test with Yates continuity correction

**An α risk of 0.05 and a β risk of 0.2 (80% power) are assumed, standard values in such studies*

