#### Design

The research is approached as a longitudinal, prospective community clinical trial. While in the conventional format of clinical trials allocation is performed on the participating subjects themselves, in the community format, clusters are assigned to which the units of analysis belong.

In this research, the clusters are the professionals of the Clinical Units of the six participating Spanish autonomous communities: Madrid, Aragon, Galicia, the Basque Country, Valencia and Catalonia (see Fig. 2). The units of analysis are the women attending the consultation of the professionals between 1 July 2019 and 30 June 2020.

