### Clusters sample

Firstly, the clusters were selected. The researchers responsible for each of the six autonomous communities in Spain recruited them by means of convenience sampling. During the first quarter of 2019, professional clinicians giving contraceptive counselling (gynaecologists, midwives, family doctors and/or nurses) from the different Spanish autonomous communities participating were invited to take part. One hundred and sixty-four (164) professionals agreed to participate and they were randomly assigned using the EPIDAT program (single sampling), to one of two groups:
Experimental Group (EG), professionals who will perform counselling with the support of the SHARECONTRACEPT SDMT, andControl group (CG), professionals who will perform clinical counselling as they had until then (conventional contraceptive counselling).

Starting from this context, it was decided to create the Web page: Sharecontracept.com, through which the professionals can easily access the three different environments in which they are to participate.

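### Professionals are randomised as clusters, but the sample size treats women as independent, so for any positive intra-cluster correlation 1708 women give less than the stated 80% power

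*Protocol article*

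**What the plan says.** The Design section of the protocol article presents a community trial in which clusters, not individuals, are allocated. It states that "the clusters are the professionals of the Clinical Units of the six participating Spanish autonomous communities". It then separates the level of analysis from the level of allocation: "The units of analysis are the women attending the consultation of the professionals between 1 July 2019 and 30 June 2020".

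The Clusters sample section gives the number of clusters and confirms that they were randomised: "One hundred and sixty-four (164) professionals agreed to participate and they were randomly assigned using the EPIDAT program (single sampling), to one of two groups".

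The Sample size section works at the level of the woman: "The calculation was performed using the EPIDAT program to test hypotheses in a model of comparison of proportions in independent groups". The note to Table 2 names the test: "Sample sizes to apply the χ2 test with Yates continuity correction". The footnote gives the error rates: "An α risk of 0.05 and a β risk of 0.2 (80% power) are assumed". The one adjustment named, in the text and in the table header, is a correction for an expected loss of 25%. The result is 854 per group and 1708 in total. Neither the number of professionals nor the number of women per professional enters the calculation, and no ICC or design effect appears.

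**The concern.** A comparison of proportions in independent groups assumes that each woman adds a full unit of information. When the professional is randomised and also delivers the counselling, women seen by the same professional are likely to resemble each other in outcome, and each adds less. The article itself supplies reasons to expect this. Its Study limitations section lists differences between regions, funding schemes, professions and levels of training. Its Discussion says that women's choices are strongly swayed by what the clinician mentions or recommends.

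This is more than a detail left to a fuller document. The article states which model it used, and that model does not match the design that it describes. At stake is the reading of the result on adherence, the main variable. If the difference is not significant, readers will weigh it against a claimed 80% chance of detecting the planned effect, and the real chance may be lower.

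**Working it through.** **Inputs from the article**
- Clusters: 164 professionals.
- Women: 854 per group, 1708 in total.
- Expected losses: 25%.
- α = 0.05, taken as two-sided because sidedness is not stated; nominal power 80%.

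**Assumptions, not in the article**
- ICC of 0.01, 0.02, 0.05 or 0.10.
- Coefficient of variation (CV) of women per professional: 0 (equal caseloads) or 0.6.

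**Step 1: the plan's own figure.** The article prints no pair of proportions, so 854 cannot be reproduced from its stated inputs. The loss step can be checked if the correction is taken as division by 1 − R: 640 / (1 − 0.25) = 853.3, rounded up to 854. The loss correction alone therefore explains the step from a base of 640 to 854. With the Yates-corrected formula, 640 per group corresponds to a difference of about 8 points near 50%: 0.46 versus 0.54 needs 637 per group, or 850 after losses. Other pairs fit about as well (for example 0.22 versus 0.29), so the planned difference cannot be recovered.

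**Step 2: women per professional**
- Recruited: 1708 / 164 = 10.4.
- Evaluable: 1708 × 0.75 = 1281; 1281 / 164 = 7.8.

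**Step 3: design effect (DE).** For equal caseloads, DE = 1 + (m − 1) × ICC with m = 7.81. For unequal caseloads, DE = 1 + ((1 + CV²) × m − 1) × ICC. With CV = 0.6 the multiplier of the ICC is 1.36 × 7.81 − 1 = 9.62.

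**Step 4: power.** If power is 80% under independence, the standardised effect is 1.96 + 0.8416 = 2.8016. Clustering divides it by √DE, so power = Φ(2.8016 / √DE − 1.96). This does not depend on the unstated proportions.

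Worked example, ICC 0.05, equal caseloads: DE = 1 + 6.81 × 0.05 = 1.34; √1.341 = 1.158; 2.8016 / 1.158 = 2.419; Φ(2.419 − 1.96) = Φ(0.459) = 0.677.

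| Assumed ICC | DE, equal caseloads | Power, equal | DE, CV 0.6 | Power, CV 0.6 |
|---|---|---|---|---|
| 0.01 | 1.07 | 77% | 1.10 | 76% |
| 0.02 | 1.14 | 75% | 1.19 | 73% |
| 0.05 | 1.34 | 68% | 1.48 | 63% |
| 0.10 | 1.68 | 58% | 1.96 | 52% |

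**Step 5: detectable difference.** Near an assumed 50% adherence, 640 women per group detect about 7.95 points with 80% power under independence. Multiplying by √DE for equal caseloads gives about 8.2, 8.5, 9.2 and 10.3 points at the four ICC values.

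**The case against.** The strongest reply is that the size of the loss is unknown. The article gives no ICC, and its clusters are many and small, which keeps the design effect modest. At ICC 0.01 power is still about 77%, and the detectable difference moves by only about 0.3 points. A reader might infer that the trial is badly underpowered. The article does not support that: only the upper part of the assumed range (0.05 to 0.10) gives a large loss. This part of the reply stands.

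It can also be said that an unreported design effect may already sit inside the base of 640. That cannot be strictly excluded, because the two proportions are not printed. But the article names the independent-groups model and one correction, for losses, and nothing in it points to a second.

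Third, the Study limitations section says that region, funding and type of professional must be taken into account in the analysis. Such adjustment could absorb part of the variation between professionals and lower the ICC that matters for power. It does not remove the remaining correlation among women of the same professional, and it does not change how Table 2 was calculated.

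A reader might also infer that recruitment should be capped at 10 or 11 women per professional. The article does not support a hard cap. If, say, 30% of professionals recruited nobody, 115 would remain active, and a cap of 11 would yield at most 115 × 11 = 1265 women, 443 short of 1708. The article does not say that the data platform could enforce a cap. A limit per professional is also an operational detail that an article may leave to the full protocol, so its absence is no fault.

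Finally, the point concerns stated power only. It does not show that the effect estimate is biased.

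**Conclusion.** The point holds. The Design and Clusters sample sections randomise 164 professionals, while the Sample size section uses a model for independent women and inflates only for losses. For any positive ICC, the 80% in Table 2 is overstated.

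The direction is certain once the ICC is above zero; the size is conditional on it. Over an assumed ICC of 0.01 to 0.10, power is about 77% down to 58% with equal caseloads, and about 76% down to 52% at an assumed CV of 0.6. The shortfall is small near 0.01 and material from about 0.02 upwards. These figures rest on a two-sided 5% test, an even spread of the 25% losses over professionals, all 164 professionals recruiting, and a nominal 80% that is correct under independence. The last of these cannot be checked without the two proportions.

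**What to change.** Keep 1708 women. In Table 2, replace the 80% with the power, or the detectable difference, of 1708 women in 164 clusters after both the design effect and the 25% losses. Print what the figure rests on:
- the two assumed adherence proportions;
- an ICC range, for example 0.01 to 0.10, with the reason for choosing it;
- the expected number of women per professional and its variation.

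Report the observed ICC with the results, so that readers can judge the power actually available. Do not add a hard cap on women per professional.

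The change needs a few lines of protocol text and no extra participants. Its downside is a less favourable stated power.

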##### Sample selection criteria

The sample will be selected from the women attending the practice of one of the professionals from either CG or EG requesting counselling on contraception or when such need is found during the stipulated period (1 July 2019 to 30 June 2020) and who fulfil the following **inclusion criteria**: have completed their primary education and be competent in Spanish and/or Catalan (the languages of SHARECONTRACEPT, although it is also in English); be between 16 and 49 years of age, have internet access, and agree to participate voluntarily in the study. **Women are excluded** who wish to have children within one year of the date of consultation or have a history of: stroke, acute myocardial infarction, thrombosis, breast cancer (< 5 years), liver cirrhosis or liver tumour.

##### Information collection questionnaires

Information on each of the women will be collected at four times during a year, from two online questionnaires developed ad hoc: an in-person survey and a telephone survey (to be conducted 3 times: at one month, at 6 months, and one year following the in-person consultation).

The main variable is adherence to treatment (compliance with the dose and method of administration and persistence in the duration of the prescribed treatment) and the secondary variables include *the woman’s sociodemographic characteristics, her medical, obstetrical and gynaecological history, her contraceptive method, decisional conflict, and variables of the professional* (see Table 3).

**Table 3 Tab3:** Variables collected in the study

Main variable	*Adherence to treatment:*
	• Compliance with dose and method of administration and
	• Persistence in the duration of the prescribed treatment
Secondary variables	*Woman’s sociodemographic characteristics:*
	• Age
	• Level of education
	• Occupation
	• Marital status/partner
	*Contact details*
	*• Telephone*
	*• Telephone 2*
	*Medical history:*
	*•* Smoker
	*•* HBP
	*•* Uterine malformations
	*Obstetric and gynaecological history:*
	*•* Menstrual pattern
	*•* Miscarriage
	*•* VTP
	*•* Living children
	*Contraceptive method*
	*•* Contraceptive method considered by the patient before counselling
	*•* Experiences with other methods
	*•* Woman’s attitude towards compliance (Morisky-Green treatment adherence test)
	*•* Contraceptive finally chosen
	*•* Incidents with the chosen method
	*•* Incident management
	Decisional conflict
	The woman’s decisional conflict in view of the choice of contraceptive method (O’Connor Scale) https://decisionaid.ohri.ca/eval_dcs.html
	And of the professional:
	*•* Satisfaction with the counsellor or clinician with the use of the digital SDMT (Likert scale)
	*•* Test of knowledge prior to and after fieldwork

**The statistical approach** will consist of a set of bivariate and multivariate descriptive analyses and the application of logistic regression models to determine the extent to which the likelihood of changing birth control method and the likelihood of choosing one particular method are linked to certain specified variables. Losses are considered as women that do not complete the follow-up of the protocol to which they were assigned or that do not to remain until the end of the analysis.

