#### 1-virtual campus

In order, insofar as possible, to standardize the procedure to be followed given that the different professional profiles and broad geographical spread, the Foundation of the Rovira i Virgili University in Tarragona (Spain) designed a 60-h online course for the professionals involved in the project.

This course is to be implemented prior to starting the fieldwork. There are two courses, one for the CG and the other for EG. The professionals of each group will receive an email with a link in order to access the corresponding SHARECONTRACEPT virtual course with a username and a password. Once inside the course, and after a brief presentation, they will be asked to perform a test of knowledge on contraception at the beginning and at the end of the course, to assess whether SHARECONTRACEPT improves the knowledge of the professionals who use it. After the first test, the system will allow them access to the rest of the course environment, where, among others, they will find forums through which they can contact the research team.

In addition, through documents and videos, they will get access to the contents of the different subjects (see Table 1), depending on whether they are professionals assigned to EG (they will be able to view the six subjects from the beginning) or CG (during the fieldwork they will only be able to view subjects 2 and 6, although they will be able to get access to the rest once sample collection has finished).

**Table 1 Tab1:** Moodle course table of contents

Theme 1	The shared decisions model
Theme 2	The SHARECONTRACEPT project
Theme 3	Which are the WHO’s eligibility criteria
Theme 4	Keys to giving good counselling
Theme 5	Videos with examples of how to counsel with the support of SHARECONTRACEPT
Theme 6	Instructions on how to implement the information collection platform of the SHARECONTRACEPT Project

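### Randomised professionals who know their arm enter the women's cases, so self-reported scales taken at the in-person survey are open to a reporting bias that differs by arm

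*Protocol article*

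**What the plan says.** All places are in the protocol article.

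- **Clusters sample.** The 164 professionals are the randomised units. The experimental group (EG) consists of "professionals who will perform counselling with the support of the SHARECONTRACEPT SDMT"; the control group (CG) counsels as before.
- **1-virtual campus, Table 1.** Theme 6 of the course is "Instructions on how to implement the information collection platform of the SHARECONTRACEPT Project". It is one of only two themes that CG can see during fieldwork; EG sees all six, including the themes on shared decisions, good counselling and example videos.
- **2- user registration.** After the course, "the professional will be requested to register with the data collection platform".
- **3-platform.** Then "access to the data collection base is granted, using a username and personal password, to start inputting cases (units of analysis"). The Design section defines the units of analysis as the women.
- **Information collection questionnaires.** The women's data come "from two online questionnaires developed ad hoc: an in-person survey and a telephone survey". There are four contacts: "an in-person survey and a telephone survey (to be conducted 3 times: at one month, at 6 months, and one year following the in-person consultation").
- **Table 3.** The secondary variables include the Morisky-Green test and "The woman’s decisional conflict in view of the choice of contraceptive method (O’Connor Scale"). Adherence is the main variable and comes from the same surveys.
- **Study limitations.** Contact between the arms is covered, as are differences between regions, funding and professions. Reporting or assessor bias is not.

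**The concern.** Decisional conflict and attitude to compliance are self-reports with no objective check. If they are given to, or entered by, the clinician who has just counselled the woman, she has a reason to answer favourably and the clinician has a reason to record it so. That alone would add noise or a shift common to both arms. The problem is that the pressure need not be equal: EG professionals have been trained in shared decision-making and deliver the new tool, while CG professionals continue as usual. A reporting difference would then coincide with arm, and adjustment for region or profession could not remove it.

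Decreasing decisional conflict is the first-named measure of improved counselling in the abstract's aims, although it is a secondary variable in Table 3. A lower score in EG is meant to support the tool, and it could not be told apart from more favourable reporting.

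**Working it through.** **1. What the text fixes and what it leaves open**

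| Question | Answer in the article |
|---|---|
| Who registers with and is trained on the platform? | The randomised professional, in both arms |
| Who inputs the cases? | The same professional, by personal log-in |
| Does that person know the arm? | Yes: EG delivers the tool; CG sees the theme on the project and counsels conventionally |
| How is the first survey taken? | In person; the calls are timed from the in-person consultation |
| Who administers that survey, and could the woman complete scales herself? | Not stated |
| At which contact is decisional conflict measured? | Not stated |
| Who makes the three calls? | Not stated |

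The first four rows together put an arm-aware counsellor in the data path at the in-person contact. That rests on stated text. That the two scales pass through this person is the natural reading, but an inference, because of the next two rows. The last row means that nothing is shown about the calls.

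**2. Size for a binary self-report (illustration)**

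The article gives no figure for this bias, so there is none to reproduce. Let p be the true favourable proportion in both arms and r the extra share of the remaining women who answer favourably in EG only. Both are assumptions, and r is set to zero in CG. The spurious gain is (1 − p) × r.

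| p | r = 0.10 | r = 0.20 |
|---|---|---|
| 0.5 | 5 points | 10 points |
| 0.6 | 4 points | 8 points |
| 0.7 | 3 points | 6 points |

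For scale: 854 per arm with 25% losses leaves 854 × 0.75 = 640.5, about 640. With 80% power and the Yates correction (both from Table 2), and assuming a two-sided 0.05 test and no clustering, the detectable increase is 8.0, 7.7 and 7.1 points from control rates of 50%, 60% and 70%. At r = 0.20 the spurious gain is therefore about as large as the effect the trial can detect; at r = 0.10 it is well below it.

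**3. Size for a scale score (illustration)**

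Assume no true effect, 640 women per arm, a two-sided 0.05 test, and a reporting shift of b standard deviations in one arm. With z = b / √(2/n), the chance of a significant difference is Φ(z − 1.96) + Φ(−z − 1.96). For clustering, n = 640 / DE, where DE = 1 + (m − 1) × ICC and m = 1708 × 0.75 / 164 = 7.8 women per professional. The ICC is assumed.

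| b | No clustering | ICC 0.01 (DE 1.07) | ICC 0.10 (DE 1.68) |
|---|---|---|---|
| 0.05 SD | 14.5% | 14% | 11% |
| 0.1 SD | 43% | 41% | 28% |
| 0.2 SD | 95% | 93% | 79% |

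Example: b = 0.1 and n = 640 give z = 0.1 / √(2/640) = 1.79 and a chance of 43%, against the nominal 5%. These figures show how small a shift would matter. They do not show that one occurs.

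**The case against.** The strongest reply is that the core fact is inferred. Inputting a case could mean no more than enrolling a woman and opening her record. Both instruments are described as online, which leaves self-completion open. A condensed article commonly leaves the interviewer's identity and access rights to the full protocol, so their absence is no error. This stands as a limit on wording and confidence. It does not remove the point, because the article does not merely stay silent: it assigns training, registration and case entry to the one person who cannot be masked.

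The illustrations are also fair game: p, r and b are assumed, and a difference between arms is built in. That stands too.

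Three stronger readings are tempting, and the article does not support them:

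- **That women in effect rate their counsellor.** The decisional conflict scale concerns the choice of method. The item "Satisfaction with the counsellor or clinician with the use of the digital SDMT (Likert scale") is listed under the professional's variables, and its wording leaves open who rates what.
- **That professionals run the platform.** They are users of a project platform.
- **That the main variable is collected at follow-up by the counsellor.** The caller is not named.

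**Conclusion.** The concern holds in a limited form. Arm-aware professionals enter the women's cases and the first survey is in person, so a reporting bias that differs by arm cannot be excluded for self-reports taken at that contact. This covers decisional conflict and the Morisky-Green test if they are given there. The direction would probably favour EG, given its training.

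The size is unknown. The 3–10 points are an assumed range for a binary self-report such as adherence and are not an estimate for the decisional conflict score. For a score, an assumed shift of 0.1 SD would raise the chance of a false significant difference to 28–43%.

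A reader might infer that adherence at 1, 6 and 12 months is biased in the same way. It comes from the same pair of surveys, but with the caller unnamed no defect is shown there. The change is worth making because it is cheap and the bias cannot be repaired in analysis. Confidence is moderate, because the step from case entry to scale entry is inferred.

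**What to change.** 1. Have the woman complete the decisional conflict scale and the Morisky-Green test herself in the existing online questionnaire. Send the link to her telephone, since Table 3 lists telephone numbers as the only contact details, and have her open it on her own device after the consultation. Internet access is already an inclusion criterion.
2. Make these answers invisible in the counsellor's log-in.
3. In the telephone surveys, hide arm and counsellor from the caller's view where the platform allows. Do not have professionals of the other arm make the calls: CG professionals could hear about the tool from EG women, which is the contamination that the Study limitations section tries to prevent.
4. State who administers each survey and at which contact each scale is given, and add reporting bias from unmasked collection to the limitations.

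The cost is a change of platform permissions and a link sent by text message. The downside is some non-response to self-completion, which a reminder at the 1-month call can limit.

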**Methods/design:**

A longitudinal, prospective-type, randomized, controlled community clinical trial, carried out in the clinical contraceptive counselling units of 6 autonomous regions in Spain, with an experimental group and a control group. Description of the intervention: The health professionals participating will be randomly assigned to one of the two groups. Clinicians assigned to the experimental group will perform contraceptive counselling assisted by SHARECONTRACEPT, and those of the control group will follow the conventional contraceptive counselling provided in their clinical unit.

It is planned to study 1708 users (control group *n* = 854 and intervention group *n* = 854), recruited from women who attend the consultations of the health professionals. The selected users will be followed up for one year. The data will be collected through ad-hoc questionnaires, and validated instruments for measuring decisional conflict and adherence to treatment.

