### Study limitations

The fact that the two groups (EG and CG) may come into contact at the same health centre or unit could result in professionals who must continue to provide counselling in a conventional manner (CG) potentially modifying how they behave if they find out about or get access to SHARECONTRACEPT due to comments by their EG peers. To avoid this insofar as possible, during training EG will be asked to keep absolute confidentiality.

Different autonomous communities, different sexual and reproductive healthcare policies, different funding schemes for contraceptive methods, different professionals giving counselling with different levels of training (midwives, nurses, gynaecologists and family physicians) could be limitations, and so these variables must be duly taken into account when analysing the results.

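### Professionals are randomised as clusters, but the only test named for comparing the groups assumes independent women, and the logistic models make no provision for clustering

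*Protocol article*

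**What the plan says.** The Design section of the protocol article sets out a community trial in which "clusters are assigned to which the units of analysis belong". It then identifies them: "In this research, the clusters are the professionals of the Clinical Units of the six participating Spanish autonomous communities". The individual women are the other level: "The units of analysis are the women attending the consultation of the professionals between 1 July 2019 and 30 June 2020". The section Clusters sample reports that 164 professionals agreed to take part and were randomised to the experimental or the control group.

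The Sample size section uses a model for two proportions in independent groups, with α 0.05, 80% power and 25% losses, and arrives at 854 women per arm. The note to Table 2 reads: "Sample sizes to apply the χ2 test with Yates continuity correction". Neither an ICC nor a design effect appears.

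The paragraph on the statistical approach, under Information collection questionnaires, lists bivariate and multivariate descriptive analyses and "the application of logistic regression models to determine the extent to which the likelihood of changing birth control method", together with the likelihood of choosing a particular method, is tied to certain variables. It mentions no random effect, GEE, robust variance or cluster-level summary.

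Study limitations lists differences in region, policy, funding and the type and training of professional, "and so these variables must be duly taken into account when analysing the results".

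**The concern.** The treatment arm is a property of the professional. All women counselled by one professional are in the same arm, and they share that professional's habits, knowledge and preferences. If their outcomes are correlated, each further woman from the same professional adds less information about the arm effect than a woman from a new one. A method that treats women as independent does not see this. It understates the standard error of the arm effect, rejects too often under the null and gives intervals that cover too little.

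The document itself gives reason to expect a positive correlation. Its Discussion says that a woman's decision depends strongly on which methods the clinician mentions or recommends, and choice of method is one of the two outcomes named for the logistic models. At stake is whether a positive result for the decision tool could be taken at the stated α of 0.05.

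**Working it through.** **Inputs from the protocol article**
- Randomised units: 164 professionals (Clusters sample).
- Planned women: 854 per arm, 1708 in total (Table 2).
- Losses: 25%. α = 0.05, power 80% (Sample size). Sidedness is not stated; two-sided is assumed here.

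**Inputs assumed**
- ICC: 0.01, 0.02, 0.05 and 0.10. Read this as the correlation that remains after any covariate adjustment.
- Equal caseloads. Unequal caseloads would raise the design effect.

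**Step 1: the plan's own figure.** If n evaluable women per arm are divided by 1 − 0.25, then 640 / 0.75 = 853.3, rounded up to 854. So 854 is consistent with 640 evaluable women per arm, 1280 in all. The 640 itself cannot be reproduced, because the expected proportions are not given.

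**Step 2: women per professional.** m = 1280 / 164 = 7.80.

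**Step 3: formulas.**
- Design effect: DE = 1 + (m − 1) × ICC.
- Factor by which a correct interval is wider: √DE.
- True two-sided type I error of a nominal 5% test: 2 × (1 − Φ(1.96 / √DE)).
- Effective number per arm: 640 / DE.

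**Step 4: results.**

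| Assumed ICC | DE | √DE | 1.96 / √DE | True type I error | Effective n per arm |
|---|---|---|---|---|---|
| 0.01 | 1.068 | 1.033 | 1.897 | 5.8% | 599 |
| 0.02 | 1.136 | 1.066 | 1.839 | 6.6% | 563 |
| 0.05 | 1.340 | 1.158 | 1.693 | 9.0% | 478 |
| 0.10 | 1.680 | 1.296 | 1.512 | 13.1% | 381 |

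Correct intervals are therefore about 3%, 7%, 16% and 30% wider than those of a method that assumes independence.

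**Step 5: does the Yates correction absorb this?** Only in part. The table is for a test whose size would be exactly 5% with independent women. At 640 per arm and an assumed proportion of 50%, the correction shifts the difference by 1/640 = 0.00156 against a standard error of √(2 × 0.25 / 640) = 0.02795, or 0.056 on the z scale. Using 2.016 in place of 1.96, the errors become about 5.1%, 5.9%, 8.2% and 12.0%. At ICC 0.01 the excess nearly vanishes; at 0.05 and above it remains. The correction does nothing for confidence intervals or for logistic regression.

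**Step 6: do the covariates in Study limitations absorb it?** Region, funding and type of professional are each shared by many professionals. Adjusting for them can lower the ICC, but it leaves the correlation among women of one professional, which is the level at which arm was assigned.

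**The case against.** The strongest reply is that the article does not state the faulty analysis. Several parts of that reply stand:

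- The text says only that logistic regression models will be applied. A mixed-effects or GEE logistic model is also one. A reader might infer that ordinary logistic regression is planned, but the text does not say so, and the variance method is often left to an analysis plan, which is not shown here.
- A reader might take the Yates chi-square to be a declared final analysis. It is named only as the test that the sample size serves.
- The logistic models are described for change and choice of method. Neither the arm effect nor adherence, the main variable, is named there.
- A reader might say that the methods assume 1708 independent women. That figure includes the allowance for losses; the calculation rests on 1280.
- The size of the effect depends on an ICC that the protocol does not give. At 0.01 to 0.02 the error is 5.8% to 6.6%, a small departure from 5%. The figure of 13.1% needs an ICC of 0.10.

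These points limit the wording without removing the conflict. Mere silence on the variance method in a condensed article would be no finding. Here, however, the article declares a cluster design and then fixes an independence-based model for comparing the groups. Nothing in the text shown corrects it, and a plan that did so would depart from the test for which the trial was sized.

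**Conclusion.** The point holds as a conditional one. The design randomises professionals, while the only group comparison that the article names assumes independent women, and its regression models carry no provision for clustering. If the arms are compared as described, standard errors are too small whenever the ICC is above 0. The direction is certain; the size is not. It rests on the assumed ICCs, on equal caseloads, on a two-sided test and on 1280 evaluable women spread over all 164 professionals.

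The documents do not support the stronger conclusion that the final analysis will ignore clustering, or that its error rate will reach the upper end of the range. The correction should still be made before the arms are compared, because it is cheap and the stated α depends on it.

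**What to change.** In the paragraph on the statistical approach, prespecify one analysis of the arm effect on adherence that respects randomisation by professional:

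- either a mixed-effects logistic model with a random intercept for professional,
- or GEE with robust variance clustered on professional.

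Choose one in advance: the first gives a conditional odds ratio and the second a marginal one, and the two differ. Adjust for autonomous community and professional type, use the same structure for change and choice of method, and fit the matching linear model for decisional conflict.

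The cost is a few sentences, little extra code and somewhat wider intervals (about 3% to 30% over the assumed ICCs). Each professional enters cases under a personal login, so the cluster identifier should be available. Table 3 does not list region or professional type, so confirm that the platform records them. A further level for health centre may need data that the article does not show to be collected, so it should not be a condition of the fix.
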